### Participants

#### Sample size

We will recruit up to 100 participants with dementia and 100 staff and carers across three data collection sites. Attrition is expected with dementia research. To counter this possibility, we will aim to over-recruit by up to 25%. It is estimated that a 95% confidence level with 5% margin of error would require N=80. We recognise that if we were running a clinical trial of effectiveness, then the number of people with dementia required would be much larger. Numbers are chosen pragmatically, reflecting the feasibility of recruitment rates within the timescale and resources of the research programme. However, this work is the first step towards a more definitive study. For a psychosocial intervention that is not a full clinical trial (as is this arts programme), this is a relatively large number of people with dementia and yields useful process data for a future, definitive study.

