#### Primary outcomes

Change over time (T1 and T2 and longer term T3) for significant improvements in the Dementia Quality of Life Scale (DEMQOL) and Holden Communication Scale will be ascertained using a repeated measures mixed-effects model. It will examine the extent to which the number of sessions attended, location, age, gender, education, socioeconomic status, medication use, Clinical Dementia Rating Scale (CDR) score and location are associated with outcomes. Differences between the three settings will be tested. Should these not be significant, data will be combined to increase sample size. Change over time in observed well-being between times 1 and 2, and differences between the control and intervention will be examined with a repeated measures mixed-effect model.

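### The stated precision (95% confidence, 5% margin, N=80) is not supported: under the usual formula with an assumed p = 0.5, 80 people give about ±11 points, and the margin is tied to no outcome

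*Protocol article*

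**What the plan says.** The Sample size section of the protocol article sets the target: "We will recruit up to 100 participants with dementia and 100 staff and carers across three data collection sites". To allow for attrition it adds "we will aim to over-recruit by up to 25" per cent. It then gives its one statement of precision: "It is estimated that a 95% confidence level with 5% margin of error would require N=80". No proportion, standard deviation, population size or estimated quantity goes with that sentence.

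The same section also says: "Numbers are chosen pragmatically, reflecting the feasibility of recruitment rates within the timescale and resources of the research programme". It accepts that a trial of effectiveness would need many more people, and it presents the work as a first step towards a definitive study.

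Under Analysis of study sample 1, Primary outcomes, the planned analysis is "Change over time (T1 and T2 and longer term T3) for significant improvements" in DEMQOL and the Holden Communication Scale, using a repeated measures mixed-effects model. Observed well-being is also modelled. These outcomes are scores, and none is a proportion.

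**The concern.** A 5% margin at 95% confidence is the familiar specification for a survey proportion, and that calculation normally leads to several hundred people. A requirement of 80 is therefore surprising. If the figure is wrong, the only precision stated for this study is too favourable. The article says the work should inform a later definitive trial, so that trial's planners are among its readers and could carry the figure forward.

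There is also a question of relevance. The margin is attached to no estimand, and the primary analyses look for "significant improvements in the Dementia Quality of Life Scale (DEMQOL) and Holden Communication Scale". Even a correctly computed margin for a proportion would not tell a reader how precisely a mean change in those scores will be estimated.

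**Working it through.** **Inputs from the article (Sample size):** 95% confidence, taken as two-sided (z = 1.96); margin e = 0.05; stated requirement 80; recruitment target up to 100; over-recruitment up to 25%.

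**Assumption not in the article:** p = 0.5, the conventional worst case.

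**1. Can the plan's figure be reproduced?**

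- Standard formula: n0 = z² p(1−p)/e² = 1.96² × 0.25 / 0.05² = 384.1, so 385. This is not 80.
- The same formula one-sided gives 270.6, so 271. This is not 80 either.
- With a finite-population correction, n = n0 / (1 + (n0 − 1)/P). For P = 100: 384.1 / (1 + 383.1/100) = 79.5, so 80. This reproduces the stated figure.
- Other populations do not: P = 125 gives 94.5, P = 200 gives about 132, and P = 1000 gives about 278. One-sided with P = 100 gives 73.2.

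The margin under that correction is 1.96 × √[(0.25/80) × (20/99)] = 0.049, in line with the stated 5%. On this reading the margin says how well a random 80 would represent 100 recruits. The study's objectives concern people living with dementia, not those 100, and people who remain after attrition are not a random sample of those recruited.

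**2. What margin do 80 people give without the correction?** The margin is 1.96 × √[p(1−p)/80].

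| Assumed p | Margin at n = 80 |
|---|---|
| 0.5 | ±11.0 points |
| 0.3 | ±10.0 points |
| 0.2 | ±8.8 points |
| 0.1 | ±6.6 points |

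At p = 0.5, 100 people would give ±9.8 points.

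**3. Do other unstated inputs give 80?** Yes, two do.

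- A proportion near 0.055 (or 0.945): 1.96² × 0.055 × 0.945 / 0.05² = 79.9.
- A mean whose SD is about 23% of its value, with a relative 5% margin: (1.96 × 0.228 / 0.05)² ≈ 80.

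The article mentions neither.

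**4. What precision applies to the actual outcomes?** Take mean T1–T2 change in a score with 80 completers.

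- Ignoring clustering: half-width = t(0.975, 79)/√80 = 1.99/8.94 = 0.22 SD of change.
- Allowing for art groups: the article plans four waves at each of three sites, so 12 groups (Intervention delivery; Focus groups). That is 80/12 = 6.67 people per group. The design effect is 1 + (6.67 − 1) × ICC, and t on 11 df is 2.20. The ICC is assumed, as the article gives none.
  - ICC 0.05: design effect 1.28; 2.20 × √(1.28/80) = 0.28 SD.
  - ICC 0.10: design effect 1.57; 2.20 × √(1.57/80) = 0.31 SD.

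**The case against.** The strongest reply is that nothing depends on the sentence. The section says the numbers were set by feasibility and disclaims an effectiveness trial. The article twice lists the lack of a randomised test as a limitation. No decision rule, power statement or analysis uses the 5%. That stands, and it makes this a correction to the reporting. It does not make the sentence true, and it remains the only precision the article gives.

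A second reply is that the derivation is not shown and may sit in a fuller protocol. Section 3 of the working gives two other sets of inputs that yield 80. So a reader might infer that 80 can only have come from treating 100 as the population, but the article does not support that certainty. The finite-population route is the only one found from numbers the article prints. The point is not that detail is missing: a bare 95% and 5%, read in the ordinary way, do not lead to 80.

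A third reply concerns p. The ±11 holds at p = 0.5, which is an assumption. At p = 0.1 the margin is ±6.6, still wider than 5, but the gap is much smaller.

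A reader might also infer that the target of 100 was derived from this figure, since 80 × 1.25 = 100. The article never makes that link and names feasibility as its basis. The over-recruitment wording could equally mean 100 × 1.25 = 125.

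**Conclusion.** The statement "95% confidence level with 5% margin of error would require N=80" is not supported and should not stand. Under the usual formula with p = 0.5, the requirement is 385 and the margin at 80 is about ±11 points. The only route to 80 found from the article's own numbers takes the recruitment target as the whole population, which is not the population the objectives address. The margin also names no estimand, while the primary outcomes are changes in scale scores.

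The size of the discrepancy rests on the assumed p. The clustered half-widths rest on an assumed ICC of 0.05–0.10 and 12 equal groups. All the half-widths describe a simple T1–T2 mean change, not the full three-time-point model with covariates.

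A reader might infer that the study is too small or should recruit 385 people. The documents do not support that: the sample is openly pragmatic, and no planned analysis requires a 5-point margin. This is an error in a stated figure, not a design defect.

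**What to change.** Delete the sentence and let the pragmatic justification already in the section carry the sample size. Leave the recruitment target as it is.

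If a precision is wanted, suitable wording would be: *With 80 completers, the 95% confidence interval for mean T1–T2 change has a half-width of about 0.22 SD of change, ignoring clustering. Clustering by art group would widen it, for example to about 0.28–0.31 SD with 12 groups and an assumed intraclass correlation of 0.05–0.10.* The intraclass correlation must be labelled as an assumption.

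The cost is one sentence and no extra participants. The downside is that the precision on record becomes less favourable.

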### Study sample 1: people living with dementia

#### Recruitment procedures

Across all sites, a simple leaflet and information sheet is given to the participants and their families/carers outlining the study, and posters distributed where possible. The information sheet describes the project, their right to withdrawal at any stage and that any care received is not affected by participation or withdrawal from the project. Participants are allowed sufficient time (5 days minimum) to consider the information, before the researcher returns to answer any questions the participant may have and note whether the individual wishes to participate and give consent for participation. A prompt card, highlighting key facts about the research is provided to the nursing, occupational therapy and care staff who will assist with identifying participants based on the inclusion criteria. Efforts are made to ensure that family members/carers are informed of the study. All participants are fully debriefed and given a contact for any further questions or for making any complaints.

In site 1, care homes are identified through the partnership with Equal Arts (the community arts partner), and initial meetings are arranged to explain the study to the manager, and then with their approval the residents and staff. In site 2, participants are identified and recruited in partnership with Derbyshire Community Services NHS Trust (DCHS). There are three wards/units across two hospitals who all admit people with dementia. The main points of contact for these wards will be through the head occupational therapist and ward manager. In site 3, people living in the community are recruited through NHS general practices in the area, memory clinics and local clubs that provide services for people living with dementia.

##### Inclusion criteria

Diagnosis of dementia or evidence of age-related memory impairment.In Newcastle/Tyne and Wear—participants will be a resident in the chosen care home.In Derbyshire—participants will be a resident in the assessment unit for a minimum of 3 months.In North Wales—participants will be living in the community in rented/private housing or sheltered housing.

##### Exclusion criteria

Recent or current episode of major mental illness.End of life/terminal illness.Debilitating illness that will preclude regular attendance.Severe uncorrected sensory or communication difficulty.Inability to communicate verbally through the medium of either English or Welsh.

##### Assessing capacity and gaining informed consent

The Mental Capacity Act (MCA; 2005) states that a person must be assumed to have capacity unless it is established otherwise. To establish whether the potential participant's memory difficulties may impact on the capacity make an informed choice, capacity will be assessed by the researcher at the point it needs to be made (ie, when discussing the study with a view to gaining consent). The researcher will assess (1) the capacity to understand the information relevant to the decision to be made, (2) retain the information, (3) use or weigh the information to arrive at a choice/decision, and (4) ability to communicate a decision. In line with the MCA Code of Practice,^30^ the first three assessments are applied together. If a person cannot do any of these three things, they will be treated as unable to make the decision. The fourth only applies in situations where people cannot communicate their decision. If there is an indication of a lack of capacity, and a person is unable to give informed consent, an opinion is sought from a family member/carer/suitable person to act as a personal consultee and provide consent. Consent is regarded as a continuing process rather than a one-off decision, and willingness to continue participating will be continually checked through discussion with participants during the assessments.

##### Data collection (people living with dementia)

The following quantitative and qualitative questionnaire data are collected in a face-to-face interview by the researcher at time 1 (baseline) prior to the start of the intervention, time 2 (follow-up) at the end of the intervention and time 3 (longer term follow-up) 3 months after the time 2 assessment.
Demographic data (eg, age, gender, marital status, socioeconomic status, education, residence).Social connectedness (Lubben Social Network Scale, six items;^31^ emotional and social loneliness, six items).^32^Dementia Quality of Life.^33^ A 28-item measure of QoL designed for people with dementia.Medication use (limited to particular types of psychotropics and those prescribed for dementia).Extent of engagement with art activities (qualitative).Expectations of taking part (qualitative, baseline only).Sense of belonging to community (five items).Memory of the sessions (qualitative, follow-up only).Perceived benefits and value (qualitative, follow-up only).

##### Associated measures for people living with dementia

Clinical Dementia Rating Scale:^34^ administered at T1 only, to establish severity of the symptoms of dementia, completed by researcher.Dementia Quality of Life:^33^ a 31-item measure of QoL designed for carers of people with dementia (to be completed by carer or staff).Holden Communication Scale:^35^ assesses a range of social, behaviour and communication variables (to be completed through discussion with carer or staff member).

##### Behavioural observation of people living with dementia

A within-participants/repeated measures 2×3 design will compare levels of well-being and engagement in two different conditions (intervention and control). The control condition is an unstructured activity. Using the Greater Cincinnati Chapter Well Being Observational Tool,^18^ observations are coded by the researcher according to the extent to which well-being and engagement are expressed at three time points: time 1, baseline (control condition only); time 2, at the start/within the first 2 weeks of intervention; time 3, the last 2 weeks of intervention. The Greater Cincinatti Chapter Well-Being Tool addresses seven domains of well-being—interest, sustained attention, pleasure, negative affect, sadness, self-esteem, and normalcy—and was developed specifically to observe the effects of visual arts on the well-being of people with dementia.

The aim of the observations in the control situations is to ensure a concurrent control for the person's function and interaction in the arts sessions, bearing in mind there may be changes over time unrelated to the project intervention. On that basis, we will undertake observations between situations within a few days of each other. Observations in each time point are carried out over 2 weeks to account for variability between sessions, as suggested by Brooker and Duce.^36^

This systematic method of observation enables an examination of the unconscious responses, that is, those that might not be verbalised during interviews. Where possible, the sessions are videoed to enable further analysis and validation. Care will be taken to ensure that others present who are not research participants cannot be identified in the filming. The videos are purely for research purposes and none of their content will be made public or shared beyond those involved in the analysis.

##### Focus groups with people living with dementia

In each of the data collection areas a short, postsession focus group is held in the last month of the intervention period with each of the intervention groups (up to 4 in each area, 12 in total). This will only be for the participants with dementia, to ensure that any effects that are experienced ‘in the moment’ are verbalised from their own perspectives. This session is led by the researcher and will be videoed or audio recorded for research purposes only, the video/audio recording is not to be made public or shared beyond those involved in the analysis.

##### Self-reported outcomes from people living with dementia

For those people living with dementia who are able, a short, five-item questionnaire developed by the research team is completed immediately after the end of an arts session. Each question, for example, ‘How interesting was the session?’ has a visual ‘smiley faces’ response scale, with associated scores ranging from ‘1=not great’ (sad face) through to ‘10=fantastic’ (very happy face). These will be collected at the beginning (weeks 1 and 2) and the end (weeks 11 and 12) of the 12-week intervention. This will ascertain individual ‘in the moment’ responses on interest, enjoyment, feelings, friendliness, achievement.

### Analysis of study sample 1

#### Primary outcomes

Change over time (T1 and T2 and longer term T3) for significant improvements in the Dementia Quality of Life Scale (DEMQOL) and Holden Communication Scale will be ascertained using a repeated measures mixed-effects model. It will examine the extent to which the number of sessions attended, location, age, gender, education, socioeconomic status, medication use, Clinical Dementia Rating Scale (CDR) score and location are associated with outcomes. Differences between the three settings will be tested. Should these not be significant, data will be combined to increase sample size. Change over time in observed well-being between times 1 and 2, and differences between the control and intervention will be examined with a repeated measures mixed-effect model.

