### Study sites

There are three study sites with distinct settings: site 1, residential care facilities in the North East of England; site 2, NHS hospital wards in Derbyshire; site 3, community venues in North Wales. These settings provide different cultural contexts (eg, different industrial histories, languages and organisational practices, urban and rural contrasts) and different residential and employment locations of the participants.

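### Pooling of the three settings hangs on a non-significant test that the sample size does not support; fix the model in advance and report every setting

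*Protocol article*

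**What the plan says.** In the protocol article, the Primary outcomes section for study sample 1 says that change in DEMQOL and the Holden scale from T1 to T2 and T3 "will be ascertained using a repeated measures mixed-effects model". The covariate list follows: "It will examine the extent to which the number of sessions attended, location, age, gender, education, socioeconomic status, medication use", then the Clinical Dementia Rating score and location a second time. The next two sentences are "Differences between the three settings will be tested" and "Should these not be significant, data will be combined to increase sample size". The section gives no significance level for this test. It does not say whether the test concerns levels or changes, or what is done if it is significant.

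The Study sites section describes three distinct settings and adds: "These settings provide different cultural contexts".

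The Sample size section says "We will recruit up to 100 participants with dementia and 100 staff and carers across three data collection sites", with an allowance of up to 25% for attrition, and "It is estimated that a 95% confidence level with 5% margin of error would require N=80". It gives no split by site. It also says that the numbers are pragmatic and that a trial of effectiveness would need many more people.

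**The concern.** The rule lets the data choose the analysis of the primary outcomes, and it reads a non-significant test as permission to treat the settings as one. That reading is safe only if the test would probably find a difference that matters. The settings were chosen as distinct, so a difference in response is plausible from the start.

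Three things are at stake. First, a real difference between settings may be averaged over and never reported. Second, if the test is significant and the sites are then analysed apart, the study gets three chances of a significant change where it had one, and each estimate is much less precise. Third, the rule fits poorly with the preceding sentence. Location is already a term in the mixed model, which presupposes one model over all settings, so it is unclear what a later decision to combine would change.

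**Working it through.** **The plan's own figure.** The simple formula for a proportion is n0 = z² p(1−p)/e². With z = 1.96, p = 0.5 and e = 0.05 it gives 384.2. A finite-population correction with population 100 gives 384.2/(1 + 383.2/100) = 79.5, so 80. And 80 × 1.25 = 100, the recruitment target. The values p = 0.5 and population 100 are assumptions; the article does not state them. On any reading, N=80 is a margin-of-error figure and says nothing about a comparison of three settings.

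**Inputs for the setting test.** From the article: three settings, N=80 required, up to 100 recruited. Assumed, because the article gives no figures: equal split (80/3 ≈ 27 per site; 100/3 ≈ 33), SD of change = 1, two-sided alpha 0.05, independent participants, and a comparison of change between settings. The true differences are also assumed, so a range is shown.

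**Power.** For a three-group F test, f² is the mean squared deviation of the setting means from their average, and the noncentrality is λ = N f².

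- Changes 0.5/0.25/0: f² = (0.25² + 0 + 0.25²)/3 = 0.0417, f = 0.204; at N=80, λ = 3.33.
- Changes 0.5/0/0: f² = (0.333² + 0.167² + 0.167²)/3 = 0.0556, f = 0.236; λ = 4.44.
- Changes 0.8/0.4/0: f² = (0.4² + 0 + 0.4²)/3 = 0.1067, f = 0.327; λ = 8.53.

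| True changes (SD) | Power, N=80 | Pooled, N=80 | Power, N=100 |
|---|---|---|---|
| 0.5 / 0.25 / 0 | 34% | 66% | 42% |
| 0.5 / 0 / 0 | 44% | 56% | 54% |
| 0.8 / 0.4 / 0 | 73% | 27% | 83% |

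At N=80 the test reaches 50% power at f ≈ 0.25 (one setting off by 0.54 SD, or an even spread of 0.62 SD). It reaches 80% at f ≈ 0.35 (0.75 SD, or a spread of 0.87 SD). Unequal sites can lower power: with 40/15/25 and the smallest site off by 0.5 SD it is 31%. Clustering within art groups would also lower it. Repeated measures and covariates could raise it.

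**False positives under the rule.** Suppose no setting changes at all, and a significant setting test leads to three separate site tests. The setting test is significant in 5% of studies, and in those at least one site shows a significant change about 82% of the time: 0.05 × 0.82 = 0.041. Studies that pool and show a significant pooled change add about 0.046. The total is about 0.087, against 0.05 if data are always pooled. The 0.82 and 0.046 come from simulation.

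**Precision.** The 95% half-width for a mean change is t(0.975, n−1)/√n.

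- One site alone, n=27: 2.056/5.196 = 0.40 SD.
- All participants, n=80: 1.990/8.944 = 0.22 SD.

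**Precision under the proposed model (27/27/26, change scores).** The standard error of the site-averaged change is √[(1/27 + 1/27 + 1/26)/9] = 0.1118. Times t = 1.991 on 77 df, the half-width is 0.22 SD, the same as for the pooled sample to two decimals. Each site's half-width, using the common residual SD, is about 1.991/√27 = 0.38 SD.

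**The case against.** The strongest defence is that the study disclaims a robust test of effectiveness, calls its numbers pragmatic and presents itself as a first step, so no efficacy decision rests on the pooled estimate. That stands and lowers the weight of the point. It does not justify the rule: the article still looks for significant improvement in its primary outcomes, and setting-specific estimates are useful to a later definitive study.

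Three stronger readings are tempting, and the documents do not support them.

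- A reader might infer that the pre-test makes the pooled confidence interval invalid or too narrow. For the average change it does not: in simulations of the two 0.5 SD scenarios, the interval reported after pooling covers the average about 95% of the time. It often misses an individual setting's true change, but it does so about equally often when data are always pooled. That is a property of averaging, not of the pre-test.
- A reader might infer that real differences will usually be lost. This depends on their size, and the article gives neither an SD nor an expected difference. An even 0.8 SD spread is pooled in only about 27% of studies at N=80, and at N=100 a single setting off by 0.5 SD is detected slightly more often than not.
- A reader might infer that a significant test reduces the study to three analyses of about 27 people. That branch is not written, the equal split is an assumption, and location as a model term would allow a single model for everyone.

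It is also fair to say that the setting question is not ignored, since a test is planned. Whether that test concerns levels or changes may be settled in a fuller document.

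**Conclusion.** The concern holds in moderate form. The article fixes a data-dependent pooling rule for its primary outcomes, and the test behind it has about 34% to 44% power at N=80, and 42% to 54% at N=100, for setting differences of 0.5 SD. Non-significance is therefore weak evidence of similar response, and small to moderate differences would often be pooled and may go unreported. If the unwritten branch means separate site analyses, the chance of at least one false significant change is about 9% rather than 5%, counting any significant site as a finding, and half-widths widen from 0.22 to 0.40 SD.

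These sizes rest on an equal split, unit SD of change, alpha 0.05 and independent participants. The qualitative point, that a test which was not sized should not decide the model, does not depend on them. It should be corrected, but it is not critical in a study that does not claim to be definitive.

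**What to change.** Delete the conditional sentence on combining data. State instead that one repeated measures mixed model is fitted to all participants, with setting and setting-by-time always included. Report the site-averaged change and the three setting-specific changes, each with a 95% confidence interval, whatever the interaction p-value. List location once.

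Add a note on interpretation. The carer-rated DEMQOL and the Holden scale are completed by or with a carer or staff member, and the recruitment section for study sample 2 takes professional staff at sites 1 and 2 but a spouse, relative or friend at site 3. For those measures, setting also carries informant type.

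The cost is a change of wording and four interaction parameters, (3 − 1) settings × (3 − 1) times. No new data are needed, all participants stay in the analysis, and the half-width for the average change remains about 0.22 SD.

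### The stated change analysis of observed well-being stops at observation time 2, the first fortnight of the programme, so it cannot show whether the intervention-control difference grows, holds or fades

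*Protocol article*

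**What the plan says.** Three parts of the Protocol article bear on this.

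- **Behavioural observation of people living with dementia.** The design is introduced thus: "A within-participants/repeated measures 2×3 design will compare levels of well-being and engagement in two different conditions". The observation times are "time 1, baseline (control condition only); time 2, at the start/within the first 2 weeks of intervention; time 3, the last 2 weeks of intervention". Control observations are to be made within a few days of the arts-session observations, with the reason given as "bearing in mind there may be changes over time unrelated to the project intervention".
- **Analysis of study sample 1, Primary outcomes.** For this outcome: "Change over time in observed well-being between times 1 and 2, and differences between the control and intervention will be examined", using a repeated measures mixed-effects model. Time 3 is not named. The same paragraph does name all three times for the questionnaire outcomes: "Change over time (T1 and T2 and longer term T3) for significant improvements in the Dementia Quality of Life Scale (DEMQOL" and the Holden scale.
- **Data collection (people living with dementia).** The questionnaires follow a different schedule, with "time 2 (follow-up) at the end of the intervention" and time 3 falling three months after that.

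No other section gives a quantitative analysis of the time 3 observations. The Secondary outcomes section says only that self-report data will be integrated with the focus group and observation data.

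**The concern.** Time 2 means different things in the two schedules. For the questionnaires it is the end of the programme. For the observations it is the beginning. Read on the observation schedule, the stated change analysis compares a point before the programme with its first fortnight and does not reach the end of the 12 weeks.

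Observed well-being is the one primary outcome for people with dementia that has a control condition. DEMQOL and Holden are followed over time without one. The article accepts that it has no randomised comparison, so the within-person contrast between arts sessions and unstructured activity carries much of the weight for the well-being objective. If its change analysis ends in the first fortnight, the controlled evidence on time course is missing, although the observations needed for it are scheduled.

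**Working it through.** **Inputs.** The observed cells come from the Behavioural observation section. The times in the change analysis come from the Primary outcomes section. No sample size, alpha, standard deviation or effect size is needed for the main check. The article gives no figure for this analysis, so there is none to reproduce.

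**Step 1: count the cells.** Write C for control, I for intervention, and 1 to 3 for observation time.

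| | Time 1 (baseline) | Time 2 (first 2 weeks) | Time 3 (last 2 weeks) |
|---|---|---|---|
| Control | C1 | C2 | C3 |
| Intervention | none | I2 | I3 |

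A full 2×3 layout has 2 × 3 = 6 cells. The schedule gives 6 − 1 = 5. Restricting to times 1 and 2 leaves three: C1, C2 and I2.

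**Step 2: what can be estimated.** A contrast of cell means is estimable without further assumptions only if it uses observed cells alone. A matrix-rank check on the cell means gave:

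| Contrast | Times 1 and 2 only | Times 1 to 3 |
|---|---|---|
| Control change, C2 − C1 | yes | yes |
| Condition difference at time 2, I2 − C2 | yes | yes |
| Intervention change from time 1, I2 − I1 | no | no |
| Condition-by-time, times 1 to 2, (I2 − C2) − (I1 − C1) | no | no |
| Condition difference at time 3, I3 − C3 | no | yes |
| Intervention change, I3 − I2 | no | yes |
| Condition-by-time, times 2 to 3, (I3 − C3) − (I2 − C2) | no | yes |

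The last row is the one that says whether the intervention-control difference grows, holds or fades. It needs time 3. The two contrasts that involve I1 stay out of reach in any case, because no arts session exists before the programme starts. A model without an interaction term would return one common time effect, but equal change in the two conditions would then be assumed and not tested.

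**Step 3: precision, as a side point.** Let D2 = I2 − C2 and D3 = I3 − C3, with equal variances, complete pairs and correlation r. Then

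SE of the average of D2 and D3 ÷ SE of D2 alone = sqrt((1 + r)/2).

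- r = 0: sqrt(0.50) = 0.71, an SE 29% smaller
- r = 0.5: sqrt(0.75) = 0.87, 13% smaller
- r = 0.8: sqrt(0.90) = 0.95, 5% smaller

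The values of r are assumptions, since the article gives none. The average over the programme is also a different quantity from the first-fortnight difference, so the ratio does not compare like with like.

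**The case against.** Several points on the other side are sound.

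- **Time 3 is not shown to be discarded.** A reader might infer that the end-of-programme observations go wholly unused. The text does not support that. The limit to times 1 and 2 attaches to change over time, while the clause on control versus intervention names no times. Time 3 could enter there, but the article does not say that it does.
- **It may be a slip.** The preceding sentences of the analysis paragraph use the questionnaire schedule, on which times 1 and 2 are start and end of the intervention. The authors may have meant start to end here too. In that case the intended plan is sound and the stated one is wrong, so the text still needs correcting.
- **No confounded comparison is planned.** A reader might infer that control at time 1 is to be compared with intervention at time 2. The article nowhere proposes this, and it schedules concurrent control observations because of possible time trends. The contrast at time 2 is a proper concurrent one.
- **The empty baseline cell is not a defect.** It is disclosed and unavoidable, and a mixed model handles five cells. Calling the layout 2×3 is loose, but the same paragraph states the exception.
- **The study is not silent on in-session change.** Self-reports are collected in weeks 1 and 2 and again in weeks 11 and 12. They have no control condition, so they do not replace the time 3 contrast.
- **The study is a first step.** The article says it is not a trial of effectiveness. That lowers the stakes but does not reconcile the two sections.

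An article may leave model detail to a fuller document. Here, however, it states which times enter the change analysis, and that statement does not fit its own schedule.

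**Conclusion.** The point holds for the change-over-time analysis. As written, that analysis ends in the first fortnight and uses three of the five scheduled cells. From these, neither intervention-condition change nor a condition-by-time effect can be estimated. It therefore cannot show how the intervention-control difference develops over the programme. This follows from the schedule and the stated times alone and rests on no assumed figure.

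It remains open whether time 3 enters the condition comparison, and whether the wording is deliberate or a slip between the two schedules. Correction is needed in either case. The precision gain from using both times is uncertain: 5% to 29% for correlations from 0.8 down to 0, under equal variances and complete pairs. It is not the main reason for the change.

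**What to change.** In the Primary outcomes section for study sample 1:

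1. Replace the reference to times 1 and 2 with observation times 1, 2 and 3.
2. State that the mixed model is fitted to the five observed cells, with time 1 as a control-only baseline. Name the intervention-minus-control difference at times 2 and 3, and its change from time 2 to time 3 (the condition-by-time contrast).
3. Label the observation times differently from the questionnaire times, for example O1 to O3, here and in the Behavioural observation section.

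The cost is a few words. The observations are already scheduled, so no new data are needed. The change should be made before the observation data are analysed, so that the choice of times cannot depend on the results.
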